**3.3 Subject withdrawal/discontinuation criteria:**

1. Inappropriate enrollment. Those who have not received any treatment after enrollment should withdraw immediately, and the subject's information will not be included in the study analysis. If the subject has already received study treatment, the investigator will evaluate the subject and determine the benefit and risk of the subject before deciding whether to withdraw. If the subject needs to be excluded, he/she will be withdrawn from the study after the completion of follow-up after treatment. The subject’s information will not be included in the efficacy analysis of this study, but should be included in the safety analysis.
2. Any of the following situations occur during the pre-treatment evaluation stage: new or deteriorated systemic disease which meet the exclusion criteria, voluntarily withdraw consent or lost to follow-up or death; poor compliance.
3. For those who are considered to be excluded by investigators, the investigator shall report the reasons for the exclusion to the principal investigator. When permitted, patients who have not yet received any study treatment should be withdrawn immediately, and the information of this subject will not be included in the study analysis. If the subject has already received the protocol specified treatment, he/she will be withdrawn from this study after the completion of the follow-up after treatment, and the subject will not be included in the efficacy analysis of this study, but should be included in the safety analysis.
4. Subjects may request withdraw from the clinical trial at any time during the study period if they do not want to continue.
5. If serious adverse events occur, the subject might be withdrawn on the judgment of the investigator.
6. Deterioration during the trial, which may threaten the life of the subject, or other conditions that may affect the observation appear during the trial.
7. The subject lost follow-up or die during the treatment period.
8. The subject received chemotherapy, Chinese medicines, other immunotherapy drugs, radiotherapy sensitizers, or other drugs that affect the efficacy and toxicity evaluation during the trial.
9. Serious deviations which makes it difficult to evaluate the drug effect.
10. Poor compliance.
11. **Study plan and timing of procedures**

[figure not shown]

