**6 Statistical analysis**

**6.1 Calculation of sample size**

This study uses the objective response rate (ORR) as the primary end point. This single-arm study requires 56 eligible patients. Considering a 10% dropout rate, a total of 63 patients will be enrolled.

The research hypothesis is based on Checkmate 017 and Checkmate 057 study, which reported an ORR of 20%. If the ORR of the experimental treatment in this study is 20%, it is not worthy of further study. But if the ORR of the experimental treatment in this study is 38%, the study is considered successful. The purpose of this study is to distinguish ORR between 20% and 38%. The statistical assumptions are: the null hypothesis ORR<=20%, and the opposite hypothesis ORR>=38%. If 17 or more of the 56 eligible patients are CR or PR, this study is deemed successful and is worthy of further study. With a one-sided type one error rate (alpha) equal to 0.0432, this study has at least 90% statistical power to reject the null hypothesis.

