**6.2 Safety Run-in**

In this study, dose-limiting toxicity (DLT) includes the following three conditions and asymptomatic biochemical abnormalities without clinical significance are not included:

(1) Grade 3 toxicity lasts for more than 7 consecutive days;

(2) Grade 4 toxicity

(3) Grade 5 toxicity that could not be ruled out the association with the trial treatment

To prevent the experimental treatment from causing excessive toxicity to patients, we will monitor the toxicity of the first 20 patients receiving the experimental treatment. Within 30 days after the first dose of sintilimab and GM-CSF, if 7 or more of these 20 patients develop any of the pre-defined DLTs, enrollment will be suspended immediately. After reviewing the data and other details, the research team will decide whether to revise the trial's treatment plan to reduce the incidence of DLT or to terminate the entire trial. This safety run-in phase of the trial has the following statistical characteristics. In this treatment scenario, it is assumed that a DLT rate of 25% or lower is acceptable, while a DLT rate of 45% or higher is not acceptable. When the DLT rate is equal to 25%, the probability of termination of the test in the Run-in phase is 0.1018; when the DLT rate is equal to 30%, the probability of termination of the test in the Run-in phase is 0.7480. In addition, if there are more than 4 deaths caused by treatment in the first 20 treated patients within the first 60 days of treatment, the trial will be stopped immediately and investigation will be carried out.

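### The run-in rule in section 6.2 counts DLTs over the first 20 treated patients without requiring completed 30-day observation, so any patient lost early without a DLT can only lower the chance of suspension

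*Protocol*

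**What the plan says.** Protocol section 6.2 sets the cohort: "we will monitor the toxicity of the first 20 patients receiving the experimental treatment". The DLT window is "Within 30 days after the first dose of sintilimab and GM-CSF". The rule is that "if 7 or more of these 20 patients develop any of the pre-defined DLTs, enrollment will be suspended immediately". The design rates are that "a DLT rate of 25% or lower is acceptable, while a DLT rate of 45% or higher is not acceptable". Two stopping probabilities are printed: "When the DLT rate is equal to 25%, the probability of termination of the test in the Run-in phase is 0.1018" and "when the DLT rate is equal to 30%, the probability of termination of the test in the Run-in phase is 0.7480". The section does not define a DLT-evaluable patient, does not make completed observation a condition for counting, and does not provide for replacement.

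Section 3.3 lists the ways a patient can leave. They include withdrawal at the patient's own request (item 4) and item 7, "The subject lost follow-up or die during the treatment period".

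Other sections bear on how far observation continues:
- Sections 7.1 and 7.4.1 collect adverse events from consent to 90 days after the last administration.
- Section 3.3, items 1 and 3, keeps treated patients whom the investigator excludes until post-treatment follow-up is complete, and retains them in the safety analysis.
- Section 5.3 requires blood counts on days 5, 9 and 14, and Table 1 requires an evaluation before the second sintilimab cycle.
- Section 7.4.3 (new anti-tumor treatment) limits recording to drug-related serious events once another therapy starts.

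Section 6.1 contains the only attrition figure: "Considering a 10% dropout rate, a total of 63 patients will be enrolled".

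**The concern.** A stopping rule written as a count out of a fixed number works as intended only if each of those patients could show the event. Here the denominator is fixed by receipt of treatment, not by observation. A patient who withdraws consent or is lost before day 30 without a recorded DLT occupies a place and cannot move the count toward the boundary. The first DLT category makes this concrete: grade 3 toxicity must last more than 7 consecutive days, so a patient lost on day 4 of such an episode has no DLT on record.

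There is a second way to fill a place without observation. The experimental treatment begins with SBRT, but the DLT clock starts at the first dose of sintilimab and GM-CSF, which section 5 allows up to two weeks later. A patient irradiated but never dosed could be one of the 20 with no DLT window at all.

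Both routes act in one direction, toward continuing enrollment. At stake is the chance that the run-in suspends a triple combination whose DLT rate is one the protocol calls unacceptable.

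**Working it through.** **Inputs.** From section 6.2: 20 patients, boundary 7, design rates 25% and 45%, and printed probabilities 0.1018 (against 25%) and 0.7480 (against 30%). Assumed, because the document gives no figure: the number *m* of the 20 who become unobserved before day 30 without a DLT.

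**Formula.** P(X ≥ r | n, p) = Σ from k = r to n of C(n,k) pᵏ (1−p)ⁿ⁻ᵏ.

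**Step 1: the printed figures.** With all 20 observed:

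| Boundary | p = 0.25 | p = 0.30 | p = 0.45 |
|---|---|---|---|
| 7 or more of 20 (as written) | 0.2142 | 0.3920 | 0.8701 |
| 8 or more of 20 | 0.1018 | 0.2277 | 0.7480 |

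Neither printed probability reproduces under the written boundary. Both match 8 or more of 20 exactly, and 0.7480 then belongs to 45%, not 30%.

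**Step 2: unobserved patients under the written boundary.** If *m* patients leave before any of their DLT risk is seen and still count among the 20, the stopping probability is P(X ≥ 7 | 20 − m, p):

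| m | Observed | p = 0.45 | p = 0.25 |
|---|---|---|---|
| 0 | 20 | 0.8701 | 0.2142 |
| 1 | 19 | 0.8273 | 0.1749 |
| 2 | 18 | 0.7742 | 0.1390 |
| 3 | 17 | 0.7098 | 0.1071 |

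At 45% the loss is 0.8701 − 0.8273 = 0.043 for one patient and 0.8701 − 0.7742 = 0.096 for two. The chance of not suspending rises from 0.130 to 0.173 or 0.226.

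**Step 3: a milder assumption.** Suppose two leavers each show half their risk before going (0.45 / 2 = 0.225). Then 18 patients have risk 0.45 and two have 0.225. With P(X ≥ 7, 6, 5 | 18, 0.45) = 0.7742, 0.8923, 0.9589:

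0.775² × 0.7742 + 2 × 0.225 × 0.775 × 0.8923 + 0.225² × 0.9589 = 0.4650 + 0.3112 + 0.0485 = 0.825.

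The loss is then 0.8701 − 0.825 = about 0.045.

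**Step 4: the other boundary.** If 8 or more of 20 is what the printed figures were built on, the value at 45% goes from 0.7480 to 0.6831 with one unobserved patient and 0.6085 with two. The direction and rough size of the effect do not depend on which boundary is meant, but the absolute figures do.

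**The case against.** The strongest reply is that the protocol does require observation across the window. A 30-day period is set, adverse events are collected well beyond it, treated patients whom the investigator excludes are followed before they leave, and visits fall inside it. Stopping treatment, poor compliance or deterioration does not by itself end DLT observation. A death whose link to treatment cannot be ruled out is itself a DLT. All of this stands. It confines the gap to patients who withdraw fully, are lost, or are never dosed. It also leaves a smaller gap for non-serious toxicity after a new anti-tumor therapy starts.

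A reader might infer that about 2 of the 20 will be lost, from the 10% in section 6.1. The document does not support that. The 10% inflates 56 eligible patients to 63 enrolled for the response-rate analysis and is not a 30-day loss rate among treated patients.

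A reader might also infer that the gate ends up weaker than designed. That is not shown. The value 0.870 appears nowhere in the protocol, and with two patients wholly unobserved the written boundary still gives 0.774, above the printed 0.7480.

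It can also be said that evaluability belongs in an analysis plan, and that section 6.2 never states that leavers score as safe. The second half is fair: this follows from the literal denominator and the section's silence. The first half carries less weight, because the rule operates during accrual and the protocol itself fixes the denominator.

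Finally, the DLT count is not the only safeguard. The same 20 patients are covered by a separate rule on treatment-caused deaths within 60 days, and section 7.5 requires serious events to be reported within 24 hours.

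**Conclusion.** The point holds in a limited form. Section 6.2 does not make completed 30-day observation, or a first drug dose, a condition for counting among the 20. Patients who become truly unobserved without a DLT can therefore only lower the chance of suspension. Under the written boundary and a 45% DLT rate, the loss is about 4 percentage points for one such patient and 10 for two, or about 5 for two who keep half their risk. These sizes rest on an assumed number of leavers, on leaving being unrelated to DLT risk, and on a boundary of 7.

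The protocol should not be read as having no observation requirement at all, nor as stating that early leavers are safe.

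The mismatch between the boundary, the rate printed as 30% and the two stopping probabilities needs no assumption. It is the firmer error in the section and must be reconciled in the same edit, since every figure above depends on it.

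**What to change.** In section 6.2, define the run-in cohort as the first 20 DLT-evaluable patients: those who received the first dose of sintilimab and GM-CSF and were then observed for 30 days, or had a DLT earlier. State that:
- patients who stop treatment but remain under observation still count;
- anyone who becomes unobserved before day 30 without a DLT, or is never dosed, is replaced in the 20 by the next treated patient;
- replaced patients who were treated stay in the safety analysis, and any toxicity recorded before they left is shown at the run-in review, because replacement could otherwise favor patients who tolerate treatment well;
- enrollment is suspended as soon as the boundary count is reached, without waiting for the cohort to fill.

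In the same edit, reconcile the boundary, the second DLT rate and the two printed probabilities so that they describe one rule.

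The cost is protocol wording. Replacements come from the 63 already planned, so no patients are added. The run-in may read out a few weeks later if one or two are replaced. Full observation also restores the chance of suspending at an acceptable 25% rate to 0.214 under the written boundary, from 0.139 with two unobserved. The team should accept that figure knowingly, as it is about twice the printed 0.1018.

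### The stopping probabilities printed for the safety run-in do not belong to the written rule of 7 or more DLTs in 20; they fit 8 or more, and 0.7480 is attached to a 30% DLT rate instead of 45%.

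*Protocol*

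**What the plan says.** Protocol section 6.2 (Safety Run-in) sets the cohort: "we will monitor the toxicity of the first 20 patients receiving the experimental treatment". DLTs are counted within 30 days of the first dose of sintilimab and GM-CSF, and the trigger is: "if 7 or more of these 20 patients develop any of the pre-defined DLTs, enrollment will be suspended immediately". A review by the research team then decides whether to change the treatment plan or end the trial.

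The design rates follow: "it is assumed that a DLT rate of 25% or lower is acceptable, while a DLT rate of 45% or higher is not acceptable". Two operating characteristics are printed. The first is given at the acceptable limit: "When the DLT rate is equal to 25%, the probability of termination of the test in the Run-in phase is 0.1018". The second, placed only five percentage points higher, reads: "when the DLT rate is equal to 30%, the probability of termination of the test in the Run-in phase is 0.7480".

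No probability is printed for 45%. A separate early stop in the same paragraph concerns treatment-caused deaths; no operating characteristics are printed for it.

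**The concern.** The printed pair is implausible on its face. The chance of stopping is said to climb from about 10% to about 75% while the true DLT rate moves by only five percentage points, and 20 patients cannot discriminate that sharply. The second probability is also given at a rate that plays no other part in the section. One would expect it at the rate named as not acceptable.

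Two things are at stake. First, these figures tell an ethics committee or investigator how the run-in behaves: how often a regimen at the acceptable limit would be halted by chance, and how reliably a too-toxic one would be caught. Second, if exactly 7 of the 20 patients have a DLT, the written rule suspends enrolment, while the rule that the figures describe does not. That disagreement is better settled before such a count arises.

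**Working it through.** **Inputs**, all from section 6.2: n = 20; trigger r = 7; acceptable rate 25%, not-acceptable rate 45%; printed probabilities 0.1018 (at 25%) and 0.7480 (at 30%).

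**Formula.** With X the number of patients with a DLT and p the true rate, P(suspend) = P(X ≥ r) = Σ C(20, k) p^k (1 − p)^(20 − k), summed over k = r to 20. Suspending as soon as the r-th DLT appears gives the same probability, because the count reaches r by patient 20 exactly when the full-cohort count would be at least r.

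**Is exact binomial the protocol's method?** In section 6.1, 17 or more responders of 56 gives a one-sided error of 0.0432 at a 20% response rate and power of 0.9076 at 38%. This reproduces the stated 0.0432 and the stated power of at least 90%, so the same method is a fair test of section 6.2.

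**Trying to reproduce the printed figures**

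| True DLT rate | 7 or more of 20 (as written) | 8 or more of 20 | Printed |
| --- | --- | --- | --- |
| 25% | 0.2142 | 0.1018 | 0.1018 |
| 30% | 0.3920 | 0.2277 | 0.7480 |
| 45% | 0.8701 | 0.7480 | none |

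The two rules differ by the single term P(X = 7), which can be checked by hand with C(20, 7) = 77,520:

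- at 25%: 77,520 × 0.25^7 × 0.75^13 = 0.1124, and 0.1018 + 0.1124 = 0.2142;
- at 45%: 77,520 × 0.45^7 × 0.55^13 = 0.1221, and 0.7480 + 0.1221 = 0.8701.

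Both printed figures therefore match 8 or more of 20 to four decimals, at exactly the two rates that the section uses to define acceptable and not acceptable.

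**Could another convention rescue the printed pair?**

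- Normal approximation for 7 or more: 0.1508 at 25% and 0.3128 at 30%; with continuity correction, 0.2193 and 0.4036.
- Poisson for 7 or more: 0.2378 and 0.3937.
- A search over all n from 5 to 63 and all cut-offs: 0.1018 at 25% occurs only for 8 of 20. Among rates of 30%, 35%, 40%, 45% and 50%, 0.7480 occurs only for 8 of 20 at 45%.
- Under 7 or more of 20, 0.7480 would need a DLT rate of about 39.9%.
- The printed rise from 25% to 30% is 0.7480 − 0.1018 = 0.6462. With 20 patients, the steepest rise at any cut-off over that interval is about 0.20 (6 or more: 0.5836 − 0.3828 = 0.2008).

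**Size of the discrepancy under the written rule**

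- At 25%: 0.2142 / 0.1018 = 2.1 times the stated probability.
- At 30%: 0.3920 / 0.7480 = 0.52 of the stated probability.
- Changing only the 30% label to 45% is not enough: the written rule would still give 0.2142 against 0.1018, and 0.8701 against 0.7480.

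**The case against.** The best defence is that the operative instruction is clear. The cut-off of 7 appears once, nothing else in the protocol contradicts it, and sites can apply it as it stands. It also suspends more often than a cut-off of 8 at any given DLT rate: 0.8701 against 0.7480 at 45%. Crossing the line leads to suspension and review, so the printed probability of termination is strictly a probability of suspension, and a false alarm need not end the trial. The twofold excess applies at exactly 25%, the upper edge of the acceptable range; the absolute risk is smaller below it. The primary response-rate test in section 6.1 is untouched.

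All of that stands. It bears on how much harm the mismatch does and leaves the printed figures wrong for the rule beside them.

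A reader might go further in three ways that the documents do not support:

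- **That patients are less protected than claimed.** At the not-acceptable rate the written rule is more sensitive than the design the figures describe. The figure printed at 30% does overstate sensitivity there, but that is an error of description.
- **That this is the trial's only early safety stop, wrongly described.** The same paragraph contains a second one, triggered "if there are more than 4 deaths caused by treatment in the first 20 treated patients within the first 60 days of treatment".
- **That the death rule is faulty too.** No probability is printed for it that could be wrong, and operating characteristics may sit in a statistical analysis plan that is not at hand. Setting 4 of 20 deaths against the 25% DLT limit compares an observed count with a true rate, and a 60-day window with a 30-day one. Section 6.2 also counts a grade 5 toxicity as a DLT when a link to treatment cannot be excluded, so such deaths within 30 days also enter the 7-of-20 rule.

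**Conclusion.** The point holds as an internal contradiction in section 6.2, with two separate errors. The cut-off and the probabilities differ by one event, and 0.7480 is assigned to 30% when it is the 8-or-more value at 45%. As a result, no probability is correctly given at the rate of which the section says "a DLT rate of 45% or higher is not acceptable".

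Under the written rule, the chance of suspending a regimen at the acceptable limit is 21%, not 10%. The chance at a 30% rate is 39%, not 75%. At 45% it is 87%.

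These values assume 20 evaluable patients with independent outcomes and a common DLT rate. Section 6.1 shows that exact binomial is the protocol's own method, and no approximation tried recovers the printed pair.

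The exact match to 8 of 20 may tempt a reader to conclude that 8 was the intended cut-off. It shows only which rule the figures were computed for; the documents do not show whether the rule or the figures carry the mistake.

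**What to change.** The sponsor should establish which element of section 6.2 is in error and make rule and figures agree:

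- **If the written cut-off of 7 stands:** restate the probabilities as 0.2142 at 25% and 0.8701 at 45%, with 0.3920 at 30% if that rate is kept.
- **If the printed figures reflect the intended design:** the stated cut-off does not match them and must be reconciled with the 8-or-more rule they describe, and the 30% label must read 45%.

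In either case, the text should call the quantity a probability of suspending enrolment, since that is what the rule triggers.

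The cost is a wording change, with no effect on sample size or the primary analysis. The downside, if 7 stands, is that the stated false-suspension probability at the acceptable limit rises from 10% to 21%.

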**6.3 Patient recruitment**

Assuming that the monthly recruitment rate is 4-5 patients, this trial is expected to complete the recruitment of patients 13-16 months after the start of the study. The last patient was followed up for another 25 months after enrollment.

**6.4 Baseline characteristic evaluation**

Baseline data include: demographic characteristics, tumor characteristics, medical history, previous anti-cancer treatments, combined medications, vital signs, etc. For measurement data, the mean, standard deviation, median, minimum, and maximum are used for description; for count data, frequency and percentage are used for description.

**6.5 Study Endpoint**

**6.5.1 Primary endpoint**

**Overall response rate (ORR):** The ratio of the total number of patients achieving CR or PR to the total number of evaluable cases according to the RECIST1.1. The data will be expressed as a two-sided confidence interval.

**6.5.2 Secondary endpoint**

**Treatment-related adverse events (TRAE):** Treatment-related toxic reactions according to the CTCAE 5.0.

**Out-of-field (abscopal) response rate (ASR):** Out-of-field response was defined as reduced by ≥30% of the longest diameter from baseline in any un-irradiated RECIST1.1 evaluable target lesions. ASR was defined as the percentage of patients achieving out-of-field response.

**Overall survival (OS):** The time interval from the first day of enrollment to death from any cause. Patients who are still alive at the time of analysis will be censored by the date of last contact until cut-off date. The Kaplan-Meier method will be used to estimate the survival curves of the two groups, and the median OS (90% two-sided confidence interval) will be calculated.

**Progression free survival (PFS):** The time interval from enrollment to the first documentation of disease progression or death due to any cause. Patients who are still alive without disease progression until data cut-off will be censored by the time of the most recent radiographic follow-up. The Kaplan-Meier method was used to estimate the survival curves of the two groups, and the median PFS (90% two-sided confidence interval) was calculated.

